**Abstract**

**Background**

Emergence, of resistance to anti-malarials is a major challenge for effective malaria control in sub-Saharan Africa. Extensive use of chloroquine (CQ) as a monotherapy led to significant increase in levels of resistance across many malaria-endemic countries, including Ethiopia. Thus continuous and regular monitoring of drug efficacy is critical for establishing rational anti-malarial drug policies. This study therefore, assesses the therapeutic efficacy of Chloroquine(CQ) for the treatment of *Plasmodium vivax* infectionsin Northwestern, Ethiopia. **Methods**

An observational, prospective 28-days in vivo therapeutic efficacy evaluation will be conducted from July to December, 2014, in Northwest Ethiopia at Bullen health center. Patients confirmed to have monoinfection of vivax malaria, aged above 6 months will be enrolled. All subjects will be then treated with standard Chloroquine(25 mg/kg for three (3) days). Parasitological and clinical outcomes of treated patients will be evaluated prospectively on days 1, 2, 3, 7, 14, 21, and 28 during the entire follow-up period.. Data will be entered and analyzed using SPSS version 20. Kaplan-Meier survival estimate will be used to analyze therapeutic failure rate during follow-up period. The initial study endpoint will be taken as the risk of failure at 28 days by survival analysis. Changes in fever and parasite clearance will be evaluated at each follow up visit. Changes in mean haemoglobin concentrations will be computed on days 0 and 28 and quantitative variables will be compared using paired *t* test. P value of < 0.05 will be considered a significant level.

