**Introduction**

There are five species of plasmodia known to infect humans of which, *Plasmodium vivax* is the most widely distributed species responsible for 25-40% of malaria cases worldwide [1], and substantial morbidity associated with vivax malaria has been reported [2-4]. In Ethiopia, vivax malaria accounts for approximately 40% of all malaria cases, and most recently it seems, this proportion is even rising. Despite the public health importance, *P. vivax* malaria has received little attention and limited funds for research and control, since it usually produces less severe symptoms than falciparum malaria [2, 5, 6].

The current treatment for vivax malaria relies primarily upon two anti-malarial drugs, chloroquine (CQ) and primaquine (PQ), with the latter being the only effective drug against the hypnozoite stage. In areas where susceptibility to CQ is ascertained the recommended doses are CQ 25 mg/kg bw (body weight) during three consecutive days (10, 10 and 5 mg/kg bw) and Premaquine(PQ) at 0.25–0.75 mg/kg bw during 14 days [7,8]. Of course, the 14-day treatment effectively cures primary blood infections and is the most effective for preventing relapses [9]. However, in areas where CQR is substantial, it is recommended that artemisinin combination therapy (ACT) be used instead, also in combination with PQ for radical cure [8].

The first evidence of CQ resistant (CQR) to *P. vivax* began to emerge in 1989 [10, 11], 30 years after the documentation of CQR *Plasmodium falciparum*. Since, then the problem of CQR to *plasmodium vivax* continued to occur in different regions at varying degrees. For instance, in Indonesia, East Timor and Papua New Guinea, CQ-resistant vivax malaria has already reached an alarming prevalence [12]. CQR has also occurred in Latin American countries such as (Guyana, Peru and Brazil) [13]. The four clinical trials carried out in Asia (Thailand and Pakistan) and Africa (Ethiopia), for instance, showed that CQ alone (25 mg/kg over 3 days) is less effective against *P. vivax* asexual blood stages than CQ (25 mg/kg over 3 days) co-administered with PQ (15 mg of PQ base/day for 14 days) over 28 days of follow-up [14].

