The emergence of resistance to anti malarials threatens efforts towards malaria control and elimination. Resistance to Drugs has been implicated in the spread of malaria to new areas and re-emergence of malaria in areas where the disease had been eliminated. It also plays significant role in the occurrence and severity of epidemics in some parts of the world [15] and results in an ongoing diseases transmission. Therefore, there is a need to monitor, the status of drug resistance to anti-malarials on continuous and regular basis (often at 2 years interval. To do so, three main tools are used for drug resistance monitoring and assessing which includes therapeutic efficacy tests (*In* vivo*)*, in vitro tests, and analyses of molecular markers.

Therapeutic efficacy assessment according to the standard protocol of the WHO is the most useful for updating national treatment policies. These include, therapeutic assessment based on evaluation of the clinical and parasitological outcomes remains the mainstay of monitoring the efficacies of anti-malarial regimens and is recommended [16]. Measures such as parasite clearance time, fever clearance time or gametocyte clearance time in vivo and in vitro assays are used to indirectly detect any variation in parasite sensitivity thereby facilitating early warning in case of emergence of tolerance or resistance [17, 18].

In Ethiopia, Chloroquine 150 mg base tablet *OR* chloroquine syrup 50 mg base is the first line drug of choice for the treatment of vivax malaria. The ideal dose is 10 mg base/kg po immediately (Day 1), followed by 10 mg base/kg po at 24 hours (Day 2), and 5mg base/kg po at 48 hours (Day 3) for a total dose of 25 mg chloroquine base/kg over three days with a maximum total of 1,500 mg chloroquine base (maximum of 2,500 mg chloroquine phosphate salt) over three days in three divided doses [19].

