Annex-: Dosing chart of CQ

Tablets of Chloroquine 150mg base or syrup 50mg base per 5ml(note: one 250mg chloroquine phosphate salt tablet contains 150mg chloroquine base). Total dose of 25 mg base per kg over 3 days(10mg base per kg on day 1, 10 mg base per kg on day 2 and 5 mg base per kg on day 3).

| **Weight(Kg)** | **Age** | **Dosage** | | |
| --- | --- | --- | --- | --- |
| **Day 1** | **Day 2** | **Day 3** |
| 7-10 | 4-11 months | ½ tablet | ½ tablet | ½ tablet |
| 11-14 | 1-2 years | 1 tablet | 0.5 tablet | 0.5 tablet |
| 15-18 | 3-4 years | 1 tablet | 1 tablet | 1tablet |
| 19-24 | 5-7 years | 1 ½ tab | 1 ½ tab | 1 tab |
| 25-35 | 8-11 | 2 ½ tab | 2 tab | 1 tab |
| 36-50 | 12-14 | 3 tab | 2tab | 2 tab |
| 51 and above | 15 yrs and above | 4 tab | 4 tab | 2 tablets |

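### Chosen by weight, the 36-50 kg row of the chloroquine chart contradicts the 10/10/5 mg/kg rule printed above it on Days 2 and 3 at every weight in the row

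*Protocol*

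**What the plan says.** The dosing annex of the Protocol (Dosing chart of CQ) gives 150 mg base per tablet and a total of 25 mg base/kg. It splits this as 10 mg/kg on Day 1, then "10 mg base per kg on day 2 and 5 mg base per kg on day 3".

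The Introduction gives the same split twice: "during three consecutive days (10, 10 and 5 mg/kg bw", and, for the national first-line regimen, a first dose of 10 mg/kg "followed by 10 mg base/kg po at 24 hours (Day 2), and 5mg base/kg po at 48 hours (Day 3". It caps the total at 1,500 mg base. The Abstract applies the regimen to everyone: "All subjects will be then treated with standard Chloroquine(25 mg/kg for three (3) days".

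The chart beneath the annex rule has a weight column and an age column. Four of its rows matter most here:

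- The row at issue reads "36-50 | 12-14 | 3 tab | 2tab | 2 tab".
- The row for the heaviest patients reads "51 and above | 15 yrs and above | 4 tab | 4 tab | 2 tablets".
- One row for small children reads "11-14 | 1-2 years | 1 tablet | 0.5 tablet | 0.5 tablet".
- The row just lighter than the one at issue reads "25-35 | 8-11 | 2 ½ tab | 2 tab | 1 tab".

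Nothing says which column governs when weight and age point to different rows. The Independent variables section has body weight recorded on Day 0 to the nearest kilogram.

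**The concern.** The rule makes Days 1 and 2 equal and Day 3 half of either. The 36-50 kg row instead makes Days 2 and 3 equal and Day 1 larger. Staff cannot follow both the sentence and the row: by weight, a 50 kg patient is due 1,250 mg under the sentence and 1,050 mg under the chart.

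The study has one arm, and its main result is the 28-day failure risk on a regimen described as 25 mg/kg. If the chart is what staff use, the regimen given is not the one described. A reader comparing the result with other chloroquine studies would be misinformed about the dose.

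**Working it through.** **Inputs.** Tablet strength (150 mg base), the 10/10/5 rule and the tablets per row all come from the dosing annex. The dose in mg/kg is tablets × 150 / weight.

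**The 36-50 kg row (3, 2, 2 tablets = 450 + 300 + 300 = 1,050 mg)**

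| | Rule (mg/kg) | At 36 kg | At 50 kg | Difference from rule |
|---|---|---|---|---|
| Day 1 | 10 | 450/36 = 12.5 | 450/50 = 9.0 | +25% to -10%; exact at 45 kg |
| Day 2 | 10 | 300/36 = 8.3 | 300/50 = 6.0 | -17% to -40%; never exact |
| Day 3 | 5 | 300/36 = 8.3 | 300/50 = 6.0 | +67% to +20%; never exact |
| Total | 25 | 1,050/36 = 29.2 | 1,050/50 = 21.0 | +17% to -16%; exact at 42 kg |

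**Can rounding explain it?** The chart uses half tablets (75 mg).

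- Day 2 under the rule needs 360/75 = 4.8 half tablets at 36 kg and 500/75 = 6.7 at 50 kg. To the nearest half tablet that is 2½ to 3½ tablets.
- Day 3 needs 180/75 = 2.4 to 250/75 = 3.3 half tablets, that is 1 to 1½ tablets.
- The printed 2 tablets appears on neither day at any weight.
- With whole tablets only, 2 on Day 2 fits 36-37 kg and 2 on Day 3 fits 45-50 kg, so no patient fits both.

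**Step to the next row.** At 51 kg the chart gives 10 tablets = 1,500 mg, or 1,500/51 = 29.4 mg/kg. The rule there gives 25 × 51 = 1,275 mg. From 50 to 51 kg the dose rises by 1,500/1,050 - 1 = 43%. Nearest-half-tablet dosing would keep totals between 23.4 and 26.8 mg/kg over 36-60 kg, where the chart runs from 21.0 to 29.4.

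**Other rows, by weight (mg/kg, bottom to top of band)**

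| Row | Day 1 | Day 2 | Day 3 | Total |
|---|---|---|---|---|
| 7-10 kg | 10.7-7.5 | 10.7-7.5 | 10.7-7.5 | 32.1-22.5 |
| 11-14 kg | 13.6-10.7 | 6.8-5.4 | 6.8-5.4 | 27.3-21.4 |
| 15-18 kg | 10.0-8.3 | 10.0-8.3 | 10.0-8.3 | 30.0-25.0 |
| 19-24 kg | 11.8-9.4 | 11.8-9.4 | 7.9-6.25 | 31.6-25.0 |
| 25-35 kg | 15.0-10.7 | 12.0-8.6 | 6.0-4.3 | 33.0-23.6 |

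The rule is missed at every weight on Day 3 at 7-10, 15-18 and 19-24 kg, on all three days at 11-14 kg, and on Day 1 at 25-35 kg. Some of this is tablet size: at 7-10 kg the Day 3 dose is 35-50 mg, and half a tablet is the smallest piece the chart uses. Some is not: at 15-18 kg the Day 3 dose is 75-90 mg, which rounds to half a tablet, and the chart prints a whole one.

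**Effect on the result (illustration only).** The Protocol gives no weight distribution and no dose-response. Assume 5.76% failure at full dose (the earlier Ethiopian figure in the Introduction), 20-40% of patients at 43-50 kg, and a failure risk ratio of 1.0 to 1.5 in them. At most, the reported risk is 5.76% × (1 + 0.4 × 0.5) = 6.9%, a shift of 0 to 1.2 points. The 95% half-width at n = 384 is 1.96 × √(0.0576 × 0.9424 / 384) = 2.3 points. The illustration ignores patients at 36-41 and 51-59 kg, who receive more than 25 mg/kg, so it leans towards overstating the shift.

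**The case against.** **The total is ordinary band behaviour.** Any weight band overshoots at the bottom and undershoots at the top. The row's unweighted mean over its 15 whole-kilogram weights is 24.7 mg/kg, and the 11-14 kg row falls almost as low (21.4). This largely stands. A reader might infer from the 24.4 to 21.0 mg/kg at 43-50 kg that the row systematically underdoses. It does not: it overdoses below 42 kg, and the Day 3 excess offsets part of the Day 2 deficit. The contradiction lies in the daily split, which band width does not explain.

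**Age might govern.** The chart does not say. Chosen by age, anyone of 15 or over gets 1,500 mg, so a 43-50 kg adult would receive more than 25 mg/kg, not less. This stands as a limit on the finding. It does not remove it: the rule is per kilogram, and for a 12-14-year-old of 36-50 kg both columns lead to the same row.

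**Low-dose failures could be identified.** A reader might infer that, with one arm, failures on a low dose cannot be told apart from failures on the stated dose. The documents do not support that. Weight is recorded on Day 0, so once the rows are fixed each patient's prescribed mg/kg dose can be calculated and failures tabulated by it.

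**No harm to the estimate is shown.** Correct. The illustrated shift rests on assumed inputs, starts at zero and lies inside the sampling error.

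**Conclusion.** The contradiction holds. Chosen by weight, the 36-50 kg row misses the stated dose on Day 2 (17-40% low) and on Day 3 (20-67% high) at all of its weights, and half-tablet rounding does not produce it. The 450 mg step between 50 and 51 kg is a further consequence. Other rows break the daily split too, so the fault is in the chart more widely.

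This rests on the annex's own tablet strength and rule, and on weight choosing the row. It does not support a claim that the failure estimate is biased: the documents contain nothing from which to size that, and the effect is probably small. It is a minor error in a dose rule the study relies on, and cheap to correct.

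**What to change.** 1. State that body weight governs the chart.
2. Split the 36-50 kg row into narrower half-tablet bands that keep close to the 2:2:1 pattern, with doses confirmed by the responsible clinicians. For example:

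| Weight | Tablets, Days 1/2/3 | Total | mg/kg |
|---|---|---|---|
| 36-39 kg | 2½ + 2½ + 1½ | 975 mg | 27.1-25.0 |
| 40-45 kg | 3 + 3 + 1½ | 1,125 mg | 28.1-25.0 |
| 46-50 kg | 3½ + 3½ + 1½ | 1,275 mg | 27.7-25.5 |

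These bands are deliberately rounded up so that no one falls below 25 mg/kg. Their mean is 26.4 mg/kg, and they differ from nearest-half-tablet dosing at 7 of the 15 weights (36-37, 40-41 and 46-48 kg). A step from 1,275 to 1,500 mg remains at 51 kg.

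3. Check the remaining rows against the rule in the same way, including 7-10, 11-14, 15-18, 19-24 and 25-35 kg. For small children the listed syrup (50 mg per 5 ml) at 1.0, 1.0 and 0.5 ml/kg meets the rule exactly.
4. If the printed rows are intended, replace 25 mg/kg with the weight-banded range they give, about 21 to 33 mg/kg for 7-60 kg (21.0 at 50 kg, 33.0 at 25 kg). Report each patient's mg/kg dose from the Day 0 weight.

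The cost is an edit to one annex table. Against the present 7 tablets, the example uses ½ fewer at 36-39 kg, ½ more at 40-45 kg and 1½ more at 46-50 kg. No new measurement is needed.

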**Inclusion criteria:**

- Patient’s age  6 months old
- Uncomplicated *P. vivax* malaria (mono- infection with *P. vivax*)
- Parasite density >250/µ1
- Rectal/ tympanic temperature 38 0c or axillary temperature 37.50c or recorded history of fever with in the preceding 24 hrs
- Ability to tolerate oral chemotherapy
- Informed consent by the patient or the legal representative
- Resident in the study area

**Exclusion criteria:**

- Adequate anti-malarial treatment within the previous 7 days
- Mixed plasmodium (*P.falciparum* + *p. vivax* or other) infection
- Danger signs (Unable to drink: repeated vomiting: recent history of convulsions: Lethargic or unconscious state: Unable to stand up or to sit) and signs of severe malaria as defined by the WHO.
- Any other known severe underlying disease (e.g. cardiac, renal, hepatic diseases, Malnutrition, known HIV infection)
- Concomitant disease masking assessment response.
- History of allergy or intolerance against study medication
- Pregnancy/Lactation
